**11b. Data Management Responsibilities**

Data management will be overseen by a dedicated data team, leading research assistants in entry, management, and monitoring of study data, in accordance with standard operating procedures. Under the guidance of the study PI, the team will also be responsible for data cleaning, and interim analyses.

**11c. Data Capture and Storage Methods**

- All *primary collected and abstracted data* will be entered into a RedCap study database for storage and management. Data collection will be done using phones/ tablets using tools developed through the mobile RedCap. All Study Staff will be trained in data protection and privacy. RedCap databases are encrypted and enabled with 2-step verification to restrict user access. The link between study identifiers and patient IDs will be securely stored in the REDCap database. The link between patient identifiers and Study ID codes will be retained until completion of the study.
- The methods of *EMR data* abstraction will follow a data use agreement between the study team and NASCOP/study sites. We will provide a list of variables and records for a data administrator to abstract the records. We will receive data in a secure, password protected format (e.g. USB or cloud server). These data will be stored in a password-protected database accessible only to authorized members of the study team.
- *Audio-recordings* will be stored on Canvas, a secured learning management system (LMS) utilized by Kenyatta National Hospital and the University of Washington. The LMS uses industry standard security and will be password protected.

**11d. Data Custody and Retrieval Procedures**

The Principal Investigator and authorized study staff will be the custodian of all the study data. Data retrieval procedures will be similar for all types of data in this study. Authorized study staff members will download the datasets from the secure servers (i.e. surveys and audio recordings) for routine quality checking and analyses. All downloaded data will be maintained on a secured, password-protected study computer.

**11e. Study Records Retention**

Retention of study records will comply with the Kenyan data laws, and the US Federal and University of Washington requirements where applicable:

(<http://f2.washington.edu/fm/recmgt/retentionschedules/gs/general/uwgsResearch#Research>).

All study data and link between participant identifiers and study ID codes in the anonymized data will be retained for 6 years following completion of the study. Audio-visual data will be destroyed after 6 years, unless a waiver has been signed. Participant consents will be retained for 6 years after the end of the study. The link between participant identifiers and study IDs will be kept under lock and key. After this time, links to identifiable data will be destroyed.

**12.** **STATISTICAL CONSIDERATIONS**

**12a. Sample Size Considerations**

**Aim 1:** *Stakeholders’ workshop:* We estimate that 40 purposively selected participants for the stakeholders’ workshop will be sufficient to provide diverse information leading to the contextual adaptation of the intervention and the implementation process. Our previous work to develop interventions in Kenya has included 30-40 stakeholders which has been sufficient to reach saturation in perspectives.

**Aim 2**: *Cluster randomized controlled trial:* From previous work, we anticipate about 25% of adolescents and young adults in each clinic will have mild to severe mental health scores and enroll in the study. We anticipate enrolling 10 to 20 participants from each of 30 sites. Table 1 contains conservative estimates of statistical power to detect a range of smaller (Cohen’s *d* = 0.2, 0.3, and 0.4) effects under different study scenarios for an alpha value of 0.05. They are conservative estimates because they assume little predictive power of covariates in the random coefficients models (i.e., R^2^ values of 0.05 for the individual level and 0.01 at the site level).

| **Table 5: Conservative power estimates** | | | | | | | | | |
| --- | --- | --- | --- | --- | --- | --- | --- | --- | --- |
|  | Intraclass correlation values | | | | | | | | |
| Number of participants per site | 0.01 | | | 0.03 | | | 0.05 | | |
| ‍ | Effect size | | | Effect size | | | Effect size | | |
|  | **0.2** | **0.3** | **0.4** | **0.2** | **0.3** | **0.4** | **0.2** | **0.3** | **0.4** |
| 10 | 0.37 | 0.69 | *0.91* | 0.33 | 0.62 | *0.86* | 0.29 | 0.56 | *0.81* |
| 20 | 0.6 | *0.91* | *0.99* | 0.48 | *0.82* | *0.97* | 0.40 | 0.73 | 0.93 |

**Aim 2:** *Implementation outcomes:* Table 6 contains the minimum detectable effects for binary and continuous implementation science outcomes under the design described above. These power estimates are for a power of 0.8, alpha of 0.05, and R^2^ = 0.05.

| **Table 6: Minimum detectable effects for implementation science outcomes** | | | | | | | |
| --- | --- | --- | --- | --- | --- | --- | --- |
| **Binary outcomes** | | | | | | | |
| ‍ | Minimum proportion difference from 0.8 | | |  | Minimum proportion difference from 0.4 | | |
| ‍ | Intraclass correlation values | | |  | Intraclass correlation values | | |
|  | 0.01 | 0.03 | 0.05 |  | 0.01 | 0.03 | 0.05 |
| Reach (~80 per site) | 0.73 | 0.71 | 0.69 |  | 0.32 | 0.30 | 0.28 |
| Maintenance (~40 per site) | 0.72 | 0.69 | 0.67 |  | 0.31 | 0.28 | 0.27 |
| Provider (~ 6 per site) | 0.60 | 0.59 | 0.58 |  | 0.20 | 0.19* | 0.19* |
| ‍Site (30) | 0.34** |  |  |  | 0.02** |  |  |
| **Continuous outcomes** | | | | | | | |
| ‍ | Minimal detectable Cohen’s d | | |  |  | | |
| Patient (~ 80 per site) | 0.16 | 0.22 | 0.26 |  |  |  |  |
| ‍Provider (~ 6 per site) | 0.43 | 0.46 | 0.48 |  |  |  |  |
| ‍Site (30) | 1.03** |  |  |  |  |  |  |

**Aim 2:** *Determinants of implementation - qualitative studies:* We will conduct up to 3 in-depth interviews (IDIs) with providers and clinic managers at intervention sites early in implementation (3-6 months) to explore early implementation outcomes and determinants of implementation. We will conduct up to 6 in-depth interviews (IDIs) and 1 focus group discussion (FGD) at each of the 30 sites with providers to assess determinants of implementation of the intervention PRO-ACT (intervention sites) and screening (all sites). Each FGD will consist of 7-10 participants, sufficient to generate conversation without being too large to become less manageable. For in-depth interviews, we will recruit 2 lower cadre staff members (e.g. peer counselor), 2 middle cadre staff members (e.g. nurse or clinical officer), and 2 managers (e.g. medical superintendent) from each facility. Based on the qualitative evaluation from past hybrid trials and the literature, we expect that 6 IDIs per site and 1 FGD per site will be sufficient to reach thematic saturation. We will also conduct up to 30 FGDs with 7-10 AYHIV participants 16-24 years from the study sites.

**Aim 3:** *Economic evaluation:* The program cost data will be extracted from project expenditure records, and collected through serial structured interviews with heads of clinics or their representatives in facilities (30). Time and motion studies will be conducted to estimate provider time offering services to AYHIV (~6 providers per facility), which will be used to reliably apportion effort to the providers implementing the activities who divide time and effort among multiple roles. The longitudinal patient survey will collect costs of seeking care from the ~600 AYHIV participating in the trial.

**12b. Planned interim analyses (if applicable)**

Analyses of the data from the stakeholders workshop, and the CQI process will inform adaptation and refinement of the PRO-ACT intervention and its delivery. No other interim analyses are planned or stopping rules.

**12c. Overview of analysis plan**

***Analysis of the effectiveness of PRO-ACT***

***Primary analyses:*** Primary analysis of the effectiveness of PRO-ACT will be conducted at 6- and 12-month follow-up. Mental health data for the primary analyses including assessments for depressive, anxiety and trauma symptoms will be collected at baseline, and follow up at months 3, 6, 9, and 12 for AYHIV with mild to moderate symptoms in intervention and control clinics. Assuming that most or all participants have completed the intervention by then, the 6-month analysis provides an estimate of the near-term treatment effect, while the 12-month analysis examines treatment effect sustainability. Both 6- and 12-month analyses will employ random coefficients models to account for clustered data structure, and compare outcome means separately (depression, anxiety, trauma) between the treatment and control groups. These models will include baseline symptom scores as predictors, as well as county, demographics, school (boarding vs. day), and clinic type (youth specific vs. integrated)as covariates. The impact of these covariates as treatment moderators will be examined. Model assumptions will be checked, including normality, linearity of effects, additional predictor interactions, and power-terms, including among baseline mental health scores (e.g., anxiety x depression interaction). We will then add provider competency to the final outcome models to examine its role as a mediator of the treatment effect.

***Secondary analyses:*** Viral load data will be abstracted from clinic records at baseline, month 6 and month 12. Viral suppression analyses at 6- and 12-month follow-ups will use similar clustered data models for the group randomized structure and strategies, as described for the analysis of the mental health outcomes, however for a binary response (i.e., relative risk regression). The same covariates and interactions will be included in the model with the treatment/control indicator variable. Model assumptions of effects and additional interactions will also be checked.

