**Aim 2: Evaluate the effectiveness and implementation of PRO-ACT for AYHIV ages 16-24 years.**

Approach: We will conduct a hybrid 1 effectiveness-implementation cluster randomized control trial in 30 HIV clinics. We will select and randomize 30 adolescent HIV clinics in Nairobi, Kisumu, and Homa Bay counties, and train non-specialist providers in 15 intervention sites. We will optimize the delivery of PRO-ACT in the intervention sites in a 6-month pretrial period using continuous quality improvement processes. Primary effectiveness outcome: Reduction in depressive, anxiety and trauma symptoms among AYHIV. Secondary outcome: Viral suppression among AYHIV. Implementation outcomes: Compare reach and describe adoption, fidelity / implementation, maintenance, acceptability and appropriateness. Identify determinants of reach, fidelity, and maintenance. Service outcomes: satisfaction of training by providers and satisfaction with services by AYHIV and providers.

*Hypothesis: The intervention will result in a significantly larger reduction of depressive, anxiety and trauma-related symptomatology over 12 months compared to the standard of care. Implementation of the intervention will improve the reach and maintenance in mental health screening and management for AYHIV.*

**Aim 3: Determine cost and cost-effectiveness of implementation for PRO-ACT training, delivery, and implementation process.**

Approach: We will conduct a time-driven activity-based costing of the intervention’s implementation strategies (training and implementation in clinics) within the 30 clinics in Kenya participating in the study to estimate the implementation costs from a patient and health system perspective. We will in addition utilize the health outcome data based on the health outcome of the intervention’s implementation in the 30 sites to estimate cost effectiveness or the intervention.

*Hypothesis: There will be an increase in costs related to the training and time for providers offering mental health services and a reduction in projected costs related to poor HIV-related and mental health. The incremental cost effectiveness ratio of the interventions will be positive.*

1. **STUDY OUTCOMES**

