**3a. Primary outcomes**

Aim 2: Cluster randomized controlled trial (cRCT)

The primary outcome for this study is **Mean change in depression scores, anxiety scores and trauma scores** measured longitudinally (5 measures) over 12 months as follows:

- Depressive symptoms: Using the Patient Health Questionnaire (PHQ-9)
- Anxiety symptoms: Using the Generalized Anxiety Disorder-7 (GAD-7)
- Trauma symptoms: Using the Child and Adolescent Trauma Screen (CATS) for AYHIV <18 years and the PTSD checklist for DSM-5 (PCL-5) for AYHIV ≥18 years

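### Six unranked primary contrasts (three scales at months 6 and 12) do not match the longitudinal outcome or the single 12-month hypothesis, and the power table covers only one unadjusted test

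*Protocol*

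**What the plan says.** Four places in the protocol bear on what the primary result is.

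- **Section 12c, Primary analyses:** "Primary analysis of the effectiveness of PRO-ACT will be conducted at 6- and 12-month follow-up". The models will "compare outcome means separately (depression, anxiety, trauma) between the treatment and control groups". The two time points are given different purposes: "the 6-month analysis provides an estimate of the near-term treatment effect, while the 12-month analysis examines treatment effect sustainability". Both sit under the primary heading, and the Protocol Summary repeats the arrangement.
- **Section 3a:** the primary outcome is mean change on the three scales, "measured longitudinally (5 measures) over 12 months". No single time point is named.
- **Section 2b, Aim 2 hypothesis:** the intervention will produce "a significantly larger reduction of depressive, anxiety and trauma-related symptomatology over 12 months compared to the standard of care".
- **Section 12a:** the power table covers "effects under different study scenarios for an alpha value of 0.05". Each cell has one effect size and one ICC. Several outcomes or time points are not mentioned.

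Section 12b plans no interim analysis of trial outcomes and no stopping rule, so month 6 is not a look within an alpha-spending scheme.

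**The concern.** Three scales at two time points give 3 x 2 = 6 treatment contrasts, all labelled primary. Section 3a points to an effect over the whole follow-up, the hypothesis to one over 12 months, and section 12c to six separate comparisons. A reader cannot tell which result decides whether the intervention works, or whether one scale is enough or all three are needed.

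The two obvious success rules fail in opposite directions. If any contrast counts, the trial can claim effectiveness under the null well above 5% of the time. If all three scales must succeed, the error rate is controlled, but the chance of success is lower than any single cell of the power table suggests. Either way, the sample-size justification does not describe the decision the trial will make.

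**Working it through.** **Inputs from the protocol.** 30 clinics, 15 per arm (section 5f). 10 or 20 participants per site, ICC 0.01, 0.03 or 0.05, d = 0.2, 0.3 or 0.4, alpha 0.05, R-squared 0.05 at individual level and 0.01 at site level (section 12a). Sidedness and dropout are not stated. The correlations between scales and between visits are not given, so they are assumed below and shown as ranges.

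**1. Reproduce the power table.** For m participants per site, the variance of the standardised difference is

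V = 4 x [ICC x (1 - 0.01) + (1 - ICC) x (1 - 0.05)/m] / 30,

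and power comes from a noncentral t with 28 df and noncentrality d/sqrt(V), for one two-sided test at 0.05.

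For m = 20, ICC = 0.03, d = 0.3:
- V = 4 x [0.0297 + 0.046075]/30 = 0.010103, so the standard error is 0.1005.
- Noncentrality = 0.3/0.1005 = 2.985; critical value 2.048.
- Power = 0.821 (stated 0.82).

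All 18 cells match to within about 0.01. Using 26 or 27 df also matches all 18. A normal approximation matches 6, omitting R-squared matches 13, and a one-sided test matches 1. The table is therefore power for one unadjusted two-sided contrast, without dropout.

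**2. Any contrast counts, each tested at 0.05.** Under independence, 1 - 0.95^6 = 0.265. With correlation, six z-statistics were simulated (400,000 draws per setting), taking the correlation between two contrasts as the scale correlation times the visit correlation, with 1 used for the same scale or the same visit.

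| Scale and visit correlations (both) | At least one false positive, six tests |
|---|---|
| 0 | 26.5% |
| 0.3 | 24.8% |
| 0.5 | 22.1% |
| 0.7 | 17.6% |
| 0.8 | 14.9% |

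For three scales at one visit, the independent value is 1 - 0.95^3 = 14.3%. It is 12.5% at scale correlation 0.5, 11.0% at 0.7 and 9.9% at 0.8. Choosing a single time point does not bring the rate to 5%.

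**3. All three scales must succeed at one time point.** With per-scale power 0.82, joint power is 0.82^3 = 0.55 if the scales are independent. By simulation it is 0.64 at scale correlation 0.5, 0.69 at 0.7 and 0.71 at 0.8.

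**4. Power when three scales share family-wise 0.05.** The strictest Holm step is 0.05/3 = 0.0167, with critical value 2.546 on 28 df. At 20 per site:

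| ICC | d | Stated, alpha 0.05 | At alpha 0.0167 |
|---|---|---|---|
| 0.01 | 0.3 | 0.91 | 0.81 |
| 0.03 | 0.3 | 0.82 | 0.67 |
| 0.03 | 0.4 | 0.97 | 0.92 |
| 0.05 | 0.3 | 0.73 | 0.56 |
| 0.05 | 0.4 | 0.93 | 0.84 |

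If all six contrasts stayed primary under Bonferroni (0.05/6), the cell at ICC 0.03 and d = 0.3 would fall to 0.56.

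**The case against.** **Multiplicity is usually left to the SAP.** Section 12c is headed as an overview and the SAP is not shown, so the absence of an adjustment method is not itself a finding. That stands. What remains lies within the protocol: it makes six contrasts primary without ranking them, defines the outcome differently elsewhere, and powers one test. An adjustment in the SAP would leave the power table mismatched to the decision rule.

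**The error rate is conditional.** The protocol never says that each contrast is tested at 0.05; that level appears only as a power input. The hypothesis, "a significantly larger reduction of depressive, anxiety and trauma-related symptomatology over 12 months", joins the three domains and can be read as requiring all of them, in which case alpha does not inflate. Both points stand, so the 15% to 26.5% applies only under an any-contrast rule. Under the other reading, the loss is in joint power.

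**The time points answer different questions.** Near-term effect and sustainability could be treated as two families of three scales, giving about 10% to 14% in each. That is fair, but neither family is placed below the other.

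**Some cells keep adequate power.** Three of the five cells in the last table stay above 0.80. The table is described as conservative, since the models also adjust for baseline scores. With individual-level R-squared of 0.25 or 0.50 (assumed), the 0.67 becomes 0.74 or 0.83. The protocol also names no target effect, so no promised power is shown to fail. The stated figures nevertheless do not describe the rule to be used.

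**Stronger readings that the text does not support.** A reader might infer that months 3 and 9 play no part, or that participants who miss month 6 or 12 are lost from the analysis. Neither is stated. Section 12c lists all four follow-up visits among the data for the primary analyses, section 3a counts five measures, and a longitudinal random coefficients model would use them all. Nor does the text make month 12 the only defensible lead: section 7e has sessions delivered within 6 months, which gives month 6 a rationale too.

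**Conclusion.** The point holds as an internal inconsistency with consequences for inference. Section 12c makes six unranked contrasts primary, section 3a describes one longitudinal outcome per scale, and Aim 2 states one 12-month hypothesis. The power table fits neither an any-scale nor an all-three rule.

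The false-positive range rests on an any-contrast rule, an inferred 0.05 per test, and assumed correlations from 0 to 0.8. The joint-power range of 0.55 to 0.71 rests on the all-three rule, the 0.82 cell, and the same assumed span of scale correlation. The mismatch with the power table depends on none of these correlations. It should be settled before outcome data are analysed, because a success rule chosen afterwards would carry little weight.

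**What to change.** Reconcile section 2b (Aim 2), section 3a, section 12c and the Protocol Summary as follows.

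1. Name one primary time point and make the other key secondary. Month 12 matches the Aim 2 hypothesis; month 6 is arguable if the hypothesis is reworded to match.
2. Estimate both contrasts from one repeated-measures mixed model per scale using months 3, 6, 9 and 12, with participants nested in clinics, treatment-by-visit terms and baseline score. This also makes explicit how the intermediate visits contribute.
3. Fix one success rule across the scales: for example Holm at family-wise 0.05, or all three required.
4. Restate the power table for that rule: at alpha 0.0167 for the first Holm step, or as joint power with the assumed scale correlation stated.

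The cost is wording and a recalculated table, with no new data. The downside is a less favourable stated power, as shown in the working.
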